#### Recruitment

Recruitment commenced in March 2024 and is planned to continue until the end of 2024. Potential participants will be identified through a range of routes depending on trust/GP practice preference, including identification via health record search, clinic attendance lists or through an opportunistic approach. Participants will receive an invitation letter, a short infographic participant information sheet and a reply form with a stamped addressed envelope (if appropriate). As interest and motivation to participate in smoking cessation studies can vary [42], those who initially decline will be offered participation up to three times, through a letter, follow‐up call and, if possible, a text message. Participants who are interested will be asked to respond to indicate this verbally over the telephone, by returning a reply slip to the research team or by using an online link to register their interest.

#### Eligibility assessment

Participants who express an interest to participate in the study will receive a telephone call from a trust/GP‐based researcher to check eligibility using a formal screening checklist and to answer any questions that participants may have about the study.

#### Consenting and baseline assessment

After verifying eligibility, participants will be invited to meet with a trust/GP‐based researcher before their scheduled clinical appointment to complete their informed consent form and baseline questionnaire in person.

#### Randomization

A computer block‐randomization method (with blocks of four and six), managed by one of the lead researchers not involved in the identification and recruitment of participants, will be used to ensure that each trial site has an equal number of intervention and control group participants. The randomization sequence will be concealed by using consecutively numbered opaque sealed envelopes that contain the allocation information. Randomization will only occur after obtaining full informed consent, completing the baseline questionnaire and the trust/GP‐based researcher completing a randomization form, which is attached to the sealed envelope. Trust/GP‐based researchers will then inform the participant and the person identified to deliver the intervention, if it is not the trust/GP‐based researcher themselves, of the allocation.

#### Blinding

Owing to the nature of the intervention and the study design, participants, researchers and clinical staff administering the intervention cannot be blinded. As the follow‐up questionnaires differ for intervention and control groups, the outcome assessment will only be blinded for questionnaires that participants complete online, rather than those completed over the phone. However, the study statistician will remain blinded to participant allocation.

#### Intervention delivery

The intervention will be delivered by a member of staff trained in delivering the intervention and should last between 5 and 10 minutes. Delivery will be performed by the trust/GP‐based researcher or by a healthcare professional as part of the scheduled clinical appointment at the site location. To increase the reach, there was a change in mode of delivery for the intervention arm in month 7, moving from adjunct appointments only to a combination of adjunct and special appointments to deliver the intervention.

#### Follow‐up data collection

Follow‐up data at 1 month and at 6 months will be obtained: online, via a link sent to the participant email address; via telephone, with support from a trust/GP‐based researcher; or via a paper‐based postal return, depending on the participant's preference. Given the alternative scenarios of intervention delivery outlined above and the potential for bias in follow‐up data collection, we stipulate that if the intervention is delivered by a trust/GP‐based researcher, then an alternative trust/GP‐based researcher will conduct the follow‐up data collection. As self‐reported abstinence at the 6‐month follow‐up will be biochemically validated using the PICO smokerlyzer (https://www.bedfont.com/products/smokerlyzer), this will require an in‐person visit either at the clinical base or in participants' homes to obtain a CO breath measurement reading to verify this.

### Measures

Table 1 presents the different measures assessed at different points throughout the trial.

#### Main outcomes

##### Primary outcomes measures

Self‐reported 7‐day point prevalence abstinence assessed 6 months after study enrolment or target quit date (for those who set a target quit date within 1 week of enrolment) and verified by exhaled breath CO < 10 ppm, which will be collected within 7 days of the 6‐month follow‐up assessment.

##### Secondary outcomes measures

Continuous abstinence at the 6‐month follow‐up, defined as not having had more than five cigarettes in the period from 2 weeks after baseline to the follow‐up, in line with the Russell Standard [40]. Self‐reported smoking abstinence at 2–4 weeks from baseline or target quit date (whichever is later). Fifty percent smoking reduction at 1‐ and 6‐month follow‐ups, calculated by the reduction in self‐reported cigarettes per day from baseline. Number of unsuccessful quit attempts at the 1‐ and 6‐month follow‐ups.

Mental health symptoms assessed by Patient Health Questionnaire‐9 (PHQ‐9) [43] and General Anxiety Disorder‐7 (GAD‐7) [44], general mood, physical symptoms assessed by the Mood and Physical Symptoms Scale (MPPS) [45, 46], and experience of adverse events at the 1‐ and 6‐month follow‐ups, similar to previous research [23].

Cost‐effectiveness of the intervention based on health economics measures outlined below.

The fidelity of intervention implementation and satisfaction with the intervention at the 1‐ and 6‐month follow‐ups will be based on questions related to e‐cigarette use in the past month as well as a question to assess whether the e‐cigarette used in the last month was the device provided to intervention participants as part of the study.

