### Objectives

#### Primary

To assess the impact of offering an e‐cigarette starter kit intervention, compared with usual care alone, on 7‐day point prevalence carbon monoxide (CO)‐validated abstinence from smoking at the 6‐month follow‐up.

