#### Secondary

To evaluate the impact of offering an e‐cigarette starter kit intervention, compared with usual care alone, on:
self‐reported continuous smoking abstinence at the 6‐month follow‐up;self‐reported smoking cessation rates at the 1‐month follow‐up;self‐reported smoking reduction at both the 1‐ and 6‐month follow‐ups;mental health outcomes and psychosocial measures at the 6‐month follow‐up.
To assess the cost‐effectiveness of offering the e‐cigarette starter kit intervention over and above usual care.To assess the adherence to and satisfaction with the e‐cigarette starter kit intervention.

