**Assessments**				
Socio‐demographic characteristics	x			
Nicotine dependence	x			
Motivation to quit	x			
Age started smoking	x			
Smoking duration	x			
Past year quit attempts	x			
Current use of tobacco products other than cigarettes	x			
Ever e‐cigarette use as smoking cessation aid	x			
AUDIT‐C	x			x
Physical activity	x			x
Fruit and vegetable consumption	x			x
Patient Heath Questionnaire‐9	x		x	x
Generalized Anxiety Disorder Scale‐7	x		x	x
7‐day point prevalence			x	x
Sustained abstinence				x
50% smoking reduction			x	x
CO breath sample				x
General mood and physical symptoms			x	x
Adverse events			x	x
Use of e‐cigarette			x	x
Healthcare service use	x		x	x
Health‐related quality of life	x			x

Socio‐demographic characteristics include age, sex, employment status, ethnicity, education, accommodation type and marital status.

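### Six-month continuous abstinence is defined by self-reported cigarette count, although the follow-up section says six-month abstinence will be CO-validated; the 1-month abstinence outcome also has two definitions

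*Protocol article*

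**What the plan says.** **Six-month abstinence.** The primary objective is "7‐day point prevalence carbon monoxide (CO)‐validated abstinence from smoking at the 6‐month follow‐up". Under Primary outcomes measures, the self-report must be "verified by exhaled breath CO < 10 ppm, which will be collected within 7 days of the" 6-month assessment.

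For continuous abstinence, the secondary objectives have "self‐reported continuous smoking abstinence at the 6‐month follow‐up". Secondary outcomes measures defines it as "not having had more than five cigarettes in the period from 2 weeks after baseline to the" follow-up and cites the Russell Standard. Neither place mentions CO.

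Follow-up data collection says that abstinence self-reported at 6 months will be validated with a CO monitor at an in-person visit. It does not say whether this means 7-day abstinence, continuous abstinence or both. Table 1 schedules one CO sample, at 6 months.

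**One-month abstinence.** The abstract and the secondary objectives give self-reported abstinence or cessation at 1 month, with no window. Secondary outcomes measures gives abstinence at 2–4 "weeks from baseline or target quit date (whichever is later". Table 1 marks "7‐day point prevalence" at 1 and 6 months, and sustained abstinence at 6 months only.

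**The concern.** The two six-month abstinence outcomes may rest on different evidence. The primary needs a breath test to agree with the participant. Continuous abstinence, as defined, needs only the participant's account.

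The Blinding section says participants and the staff delivering the intervention cannot be blinded, and that outcome assessment by telephone is not blinded either. Only the intervention arm is given a product to help with quitting. Over-claiming could therefore differ between arms, and a self-reported outcome passes that difference straight into the treatment effect. The result could then contradict the verified primary, or seem to reinforce it without independent support.

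At 1 month, two windows are in play with no rule for choosing between them, so the reported result could depend on a choice made after the data are in.

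**Working it through.** **1. The plan's own figure.** The only power statement concerns the CO-verified primary outcome. Inputs from Sample size: 308 per group, two-sided alpha 0.05, 5% versus 13.1%. The formula is

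power = Φ[(d − 1.96·se0)/se1], with se0 = √(2p̄(1−p̄)/308), se1 = √((p1(1−p1)+p2(1−p2))/308) and p̄ the mean of p1 and p2.

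- 5% v 13.1%: d = 0.081, p̄ = 0.0905, se0 = 0.0231, se1 = 0.0229, so power = Φ(1.56) = 94.1%. This agrees with the stated more than 90%.
- 5% v 11.6%: 84.5% by the same formula. With a continuity correction, 80% power needs 303 per group, close to the planned 308, so the stated 80% is also consistent.

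Nothing in this point changes these figures.

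**2. Who counts as abstinent at 6 months.** Four kinds of participant, under the definitions as written:

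| Participant | Primary | Continuous abstinence, on its own definition |
|---|---|---|
| Reports 7-day abstinence and at most five cigarettes; CO below 10 ppm | Success | Success |
| Same reports; CO 10 ppm or more | Failure | Success |
| Same reports; never attends for CO | Failure | Success |
| At most five cigarettes since week 2, one of them in the last 7 days | Failure | Success; not stated whether a CO sample is requested |

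In rows 2 and 3, the sentence in Follow-up data collection would make continuous abstinence a failure if it governs that outcome. The text does not settle this. In row 3, the rule under Primary analysis that participants without outcome data count as smoking does not clearly apply, because this participant has given the self-report on which the outcome is defined.

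Row 4 follows from the five-cigarette allowance. It means that continuous abstinence is not contained in 7-day abstinence, so the two could disagree even with full CO verification.

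**3. Illustration of size.** The article gives no misreporting rate. Assume true continuous abstinence of 5% in both arms and d extra percentage points of false claims in the intervention arm only. The self-report risk ratio is (5 + d)/5. The chance of a significant result favouring the intervention comes from the formula in step 1.

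| d (points) | Risk ratio with no true effect | Chance of significance in favour |
|---|---|---|
| 0 | 1.0 | 2.5% |
| 1 | 1.2 | 8% |
| 2 | 1.4 | 18% |
| 3 | 1.6 | 33% |
| 4 | 1.8 | 49% |

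For d = 3: p̄ = 0.065, se0 = 0.01987, se1 = 0.01983, and Φ[(0.03 − 1.96 × 0.01987)/0.01983] = Φ(−0.45) = 33%. CO verification would remove only the part of d that is due to recent smoking.

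**4. One-month window.** Weeks 2–4 and the last 7 days are different periods, so they are different outcomes. A target quit date can fall up to 7 days after enrolment. The window then closes at day 7 + 28 = 35 from enrolment. If the 1-month assessment is dated from enrolment, it comes before the window closes. If it is dated from the target quit date, the window closes 28 days later and there is no timing problem. The article does not state the origin for this visit.

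**The case against.** A reader might infer that the protocol has settled on leaving continuous abstinence unverified. The article does not support that. Follow-up data collection promises validation of self-reported six-month abstinence in general terms. The primary outcome is itself introduced as self-reported and is still CO-verified, so the word may only describe how the answer is collected before verification. Only the secondary objectives attach it to continuous abstinence. The definition also cites the Russell Standard, whose content cannot be checked here. What stands is a conflict between sections, not a decision against verification.

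A reader might also treat this as a key secondary endpoint with a known bias. The article ranks no secondary outcome as key, and the false-claim rates above are assumptions. A self-reported secondary beside a verified primary can be a legitimate choice if it is stated as one.

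Nor does it follow that everyone concerned already gives a CO reading. A person within the five-cigarette allowance who smoked in the last week may not be invited, so a CO rule with missing counted as smoking could partly cancel the allowance. This objection is sound and shapes the fix.

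On the 1-month outcome, Table 1 can be read as a collection schedule that does not redefine anything, and the day-35 difficulty depends on an origin that is nowhere stated. Both points are fair. Even so, the table has no 1-month row matching the 2–4 week outcome, and the outcome section lists no 1-month 7-day outcome.

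**Conclusion.** The point holds as an inconsistency with a practical consequence. The objectives and the outcome definition let a participant who fails or misses the CO test count as continuously abstinent, while the follow-up section can be read to rule this out. Because participants are unblinded, the choice matters for bias, but its size cannot be estimated from the article: the risk ratios of 1.4 to 1.8 rest on an assumed 2 to 4 points of one-sided over-claiming and a 5% true rate in both arms.

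The 1-month conflict between a 2–4 week window and 7-day point prevalence is also real. The claim that the window outlasts the visit is conditional on dating the visit from enrolment.

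The definitions should be settled before analysis.

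**What to change.** **Continuous abstinence.**
- Require CO below 10 ppm at the 6-month verification visit, and count a missing reading as smoking.
- Invite for CO everyone who reports either 7-day or continuous abstinence, including those within the five-cigarette allowance who smoked in the last week.
- Keep the self-report version as a sensitivity analysis.
- Align the secondary objectives, Follow-up data collection and Secondary outcomes measures.

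**One-month abstinence.**
- Choose one definition.
- State whether the 1-month visit is dated from enrolment or from the target quit date.
- Align the abstract, the secondary objectives, Secondary outcomes measures and Table 1.

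**Cost.** Mostly wording, since a 6-month CO visit is already scheduled. The downsides are a slightly lower continuous-abstinence rate and possibly a few more CO visits. The sample size does not change.

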#### Baseline measures

We will record age, sex, employment status, ethnicity, education, accommodation type and marital status (Table 2), as well as most recent diagnosis and acute events (e.g. hospitalization) in the last year based on the participants' medical records. We will also assess nicotine dependence with the Strength of Urges to Smoke Scale [47] and motivation to quit with the Motivation to Stop Scale [48]. Age started smoking, smoking duration, past year quit attempts, current use of tobacco products other than cigarettes and ever e‐cigarette use as a smoking cessation aid will also be recorded. Alcohol use will be measured using the Alcohol use disorders identification test for consumption (AUDIT‐C) [49]. Physical activity (strength training; moderate or vigorous aerobic physical activity) will be assessed with questions from the Allied Dunbar National Fitness survey [50]. Consumption of at least five portions of fruit and vegetables (Healthy Eating Index) [51] will also be recorded.

**TABLE 2 add70115-tbl-0002:** Measures of participant sociodemographic characteristics.

Characteristic	Question	Answer options
Age	What is your age?	18–99 years
Gender	What is your gender?	(i) Male (ii) Female (iii) Other
Ethnicity	How would you describe your ethnic background?	(i) White (ii) Mixed/Multiple (iii) Asian/Asian British (iv) Black/African/Caribbean/Black (v) British (vi) Chinese (vii) Arab (viii) Other
Education	What is your highest educational qualification?	(i) GCSE/O‐level/CSE (ii) Vocational qualification (iii) A‐level or equivalent (iv) Bachelor’s degree or equivalent (v) Master’s/PhD or equivalent (vi) No formal qualifications (vii) Other
Employment status	How would you describe your employment status?	(i) Employed full‐time (ii) Employed part‐time (iii) Self‐employed (iv) Retired (v) Student (vi) Voluntary worker (vii) Not employed but seeking work (viii) Not employed but not seeking work because of ill health (ix) Not employed but not seeking work for other reason (x) Other
Accommodation type	What is your current accommodation type?	(i) Purchasing with a mortgage (ii) Owned outright (iii) Rented from the local authority (iv) Rented from a private landlord (v) Rented from a housing association/trust (vi) Other
Marital status	What is your marital status?	(i) Single (ii) Married (iii) Living with partner/cohabiting (iv) Divorced/separated (v) Widowed (vi) Other

### Adverse events

At the 1‐ and 6‐month follow‐ups, participants will be asked to indicate if they have experienced any adverse events over the previous month and if these events stopped them from doing things they would normally do. These include the most common adverse events in previous trials, such as nausea, shortness of breath, throat/mouth irritation, increased appetite and headache [23].

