#### Intervention

Participants allocated to the intervention group will be offered an e‐cigarette starter kit, and a verbal explanation and demonstration, along with an information leaflet on how to use the e‐cigarette as an adjunct to the usual care outlined above. The e‐cigarette starter kit will contain a pod‐based e‐cigarette (ICON Vape), which is suction‐automated and uses pre‐filled 1.6‐mL pods containing 20 mg/mL nicotine e‐liquid. We chose a high nicotine concentration based on pervious work in this population, because smokers with mental illness have higher dependence [31] and e‐cigarettes with higher nicotine concentrations tend to be more effective [16]. All intervention participants will be provided with a 4‐week supply of refill pods (seven boxes) in tobacco, menthol and fruit flavours in a 1 : 2 : 2 ratio, based on the choice of flavour preferences observed during the feasibility study. All intervention participants will be able to choose the flavour of the final two boxes. The ICON Vape device was selected based on consumer research undertaken by the University of East Anglia [32, 33, 34], where it received high ratings for ease of use, satisfaction, taste and flavour options. All intervention participants, regardless of their motivation to stop smoking, will be encouraged to consider quitting and to set a target quit date within a week of randomization. They will be asked to start using the e‐cigarette as soon as possible and to seek out local or online vape shops to obtain further e‐liquid pods, suited to their individual needs and flavour preference. Participants who do not wish to set a target quit date will be encouraged to use the e‐cigarette to reduce cigarette consumption as soon as possible.

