### Data and safety monitoring

A trial steering committee independent of the investigators, their employing organizations, funders and sponsors will provide overall supervision of the trial. They will monitor progress and advise on scientific credibility. A data monitoring committee will assess the progress of the trial. Safety monitoring and procedure manuals will be written before the commencement of the trial and distributed to relevant research staff. All adverse events will be recorded, and recurring (i.e. occurring in multiple participants more than once during the study period) adverse events will be reported to the data monitoring committee.

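### Adverse events are asked about for only two of the six months of follow-up, which does not fit the promise to record them all

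*Protocol article*

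**What the plan says.** The Adverse events section of the protocol article sets the recall window: at each of the two follow-ups, "participants will be asked to indicate if they have experienced any adverse events over the previous month". Participants are also asked whether the events limited their normal activities. The listed examples are mostly mild symptoms such as nausea, throat or mouth irritation and headache.

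The timing is the same elsewhere. The secondary outcome is "experience of adverse events at the 1‐ and 6‐month follow‐ups, similar to previous research". Table 1 marks the row "Adverse events" at 1 month and 6 months only. Under Follow-up data collection, "Follow‐up data at 1 month and at 6 months will be obtained", and no routine contact between them is described.

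The Data and safety monitoring section is broader: "All adverse events will be recorded, and recurring (i.e. occurring in multiple participants more than once during the study period) adverse events will be reported". The recipient of those reports is the data monitoring committee. The section also says that safety monitoring and procedure manuals will be written. Their content is not given.

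**The concern.** The described questioning looks back one month from month 1 and one month from month 6. The safety section speaks of all events, and its reporting trigger is defined over the whole study period. The described data cannot fully support either.

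The months not asked about are not obviously low in interest. They begin about when the 4-week pod supply runs out and intervention participants are to "seek out local or online vape shops to obtain further e‐liquid pods". The plan also treats hospital admission for acute events as a real possibility, since it is the reason given for one exclusion criterion. The absence of mental health harm in earlier studies is part of the rationale in the Introduction.

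At stake are the adverse event secondary outcome and the safety reporting. If the results are read as six-month safety, a short admission or crisis in, say, month 3 may be absent from them. No analysis plan can recover an event that was never asked about.

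**Working it through.** **Inputs from the protocol article.** Follow-up is 6 months from enrolment, or from a target quit date set within 1 week of it (Primary outcomes measures). Adverse events are assessed at months 1 and 6 (Table 1; Secondary outcomes measures), with a recall of one month each time (Adverse events). The article states no coverage figure, so there is none to reproduce.

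**Coverage of calendar time.**
- Windows asked about: 0–1 and 5–6 months, so 2/6 = 33%.
- Not asked about: months 2, 3, 4 and 5, so 4/6 = 67%.
- If the clock starts at a quit date one week after enrolment, time from enrolment is 6 + 7/30.4 = 6.23 months. Coverage is 2/6.23 = 32% and the gap is 4.2 months.
- If a participant misses the 1-month form, coverage falls to 1/6 = 17%.

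**Other described sources.**
- Service use questionnaire (Table 3): includes A&E visits and inpatient nights, but only for the past month, so it has the same gap.
- Medical records: acute events such as hospitalization are taken for the year before baseline (Baseline measures). No record check at follow-up is described.
- PHQ-9 and GAD-7: taken at baseline, 1 and 6 months. Lasting deterioration that began in the gap could show at month 6; an episode that has resolved would not.

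**From time to events.** The share of events captured depends on their timing and duration, which the document does not give. The range is wide:
- Symptoms confined to the first month of device use fall inside the first window.
- Symptoms that persist to the last month are reported at month 6, whenever they began.
- Short-lived events spread evenly over follow-up (an assumption) fall in a window with probability 1/3.
- Events that start and resolve within months 2–5 are captured with probability 0.

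**The recurrence trigger.** Take it to mean repeated events within participants. Under the same even-spread assumption, two independent short-lived events in one participant both fall in an asked-about window with probability (1/3)² = 1/9 = 11%. On that assumption the trigger cannot be applied reliably to the questionnaire data.

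**The case against.** The strongest reply is that the two sections describe different things. One is a symptom questionnaire feeding a secondary outcome defined at two time points. The other is a safety process with its own manuals, and a journal article need not reproduce them. Spontaneous or serious-event reporting may well be set out there. This stands. A reader might infer that events in months 2–5 are recorded by no one, or that the two sections flatly contradict each other. The document supports neither: it shows only that no collection for those months is described.

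It is also fair that two snapshots are what the secondary outcome promises, that adverse events are only to be described, and that the one-month window is the same in both arms. The window by itself therefore does not bias the comparison of symptoms. A difference between arms in volunteered reports is possible in an unblinded trial, but the document gives no evidence of one.

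Nor may a reader take 67% as the share of events lost. Early and persistent symptoms are covered, and one-month recall is a defensible choice for mild ones.

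What the reply does not remove is the transient serious event. The recall window is stated outright, not left to another document, and no described instrument reaches an activity-limiting event or admission that began and resolved in the gap.

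**Conclusion.** The point holds in a limited form. The described adverse event questioning covers 2 of 6 months (32–33%, less if the 1-month form is missed), and the service use form does not fill the gap. That does not fit a statement that all adverse events will be recorded, or a trigger defined over the study period. The practical loss is transient activity-limiting events and admissions in months 2–5. Their number cannot be estimated from the document.

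The conclusion assumes that the article describes all scheduled questioning. If the manuals set out an active route for the gap, the remaining fault is that the article does not say so. The primary outcome, sample size and power are untouched. The change should be made, because it is cheap and concerns safety ascertainment.

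**What to change.** 1. On the existing 6-month form, add an item, worded identically in both arms, on events since the 1-month follow-up (since enrolment if that form was missed) that limited normal activities or led to hospital attendance. Keep the one-month window for the mild listed symptoms. Coverage for the more serious events then rises from 2 of 6 to 6 of 6 months.
2. Mild events in months 2–5 stay unasked, so item 1 alone does not make the safety statement true. Reword the Data and safety monitoring section, including the recurrence trigger, to match what is collected, and name any other reporting route.
3. Report the symptom data as two one-month windows by arm, not as six-month safety.

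**Cost.** One item and one branch for a missed form, across online, telephone and postal modes, with less accurate recall over five months. Recruitment was planned from March to the end of 2024, so on that timetable 6-month forms fall due from about September 2024 to mid-2025. If that collection has begun, participants will have different windows, which must be flagged in the analysis. If it is complete, only items 2 and 3 apply.
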